## Abstract

**Background:**

Obesity in adults and children is increasing worldwide at alarming rates. Obese children and adolescents are likely to become obese adults with increased risk of a number of comorbidities. In addition to preventing the development of obesity at young age, it is necessary to individualize the therapy of already obese children and adolescents in order to increase the likelihood of weight loss and maintenance. Therefore, the aim of this study is to identify predictors which play a significant role in successful weight loss and weight loss maintenance in children and adolescents.

**Methods/Design:**

Over a one year period, 60 obese children and adolescents between 9 to 17 years of age shall be recruited at an inpatient children rehabilitation facility in Germany. They will be investigated twice within a few days following admission and prior to discharge. The study will be an integrated component of an established inpatient weight-loss and in part psychosomatic therapy. The collected data can be grouped into four clusters: 1) demographic, sociometric and psychometric data, 2) objective and subjective parameters of body condition, 3) autonomic nervous system regulated functions and 4) objective and subjective parameters for eating behavior. Primary outcome is the change of the body mass index standard deviation score (BMI-SDS). In order to evaluate the data appropriately, all examinations will be also conducted in a normal-weight reference group, matched for age and gender.

**Discussion:**

For some of the collected parameters the time span between measures may be too short. Therefore, a 6 months, 1 year and 2 year follow-up will be performed for evaluating the different predictors and their influence in regard to a successful intervention. Further middle- and long-term follow-up studies are planned.

**Trial Registration:**

The study protocol was approved by the Ethics Committee of the University Hospital Tübingen, Germany. This study is registered at the German Clinical Trials Register (DRKS) with the clinical trial number
DRKS00005122.

## Background

### Rationale of the study

Obesity and its associated effects are increasingly becoming a health problem worldwide – both in children and in adults
[1]. In Germany – as in most other European countries – up to 15% of the children between 3 and 17 years are overweight and 6% are obese
[2,3]. Obesity is characterized by an excessive increase in adipose tissue
[4]. According to the World Health Organization (WHO) an individual is defined as overweight with a body mass index (BMI) ≥ 25 kg/m^2^ and as obese with a BMI ≥ 30 kg/m^2^[5]. However, these ranges are not transferable to children and adolescent values because of the different phases of life as a function of growth and puberty. Therefore, in pediatric medicine gender and age specific standard value tables are used for classification. By definition children and adolescents are overweight if their value is within the top ten percent and as obese if within the top three percent of their age group
[5].

There are different inpatient and outpatient therapies to treat obesity in children and adolescents. These target changes in the fields of behavior, nutrition and physical activity
[6]. In some cases, inpatient treatment is indicated, e.g. in children with severe obesity coupled with disturbed eating behaviors and psychosocial problems. For many children, these therapies are initially successful. In addition to weight reduction parameters like physical fitness, blood pressure, lipid and insulin levels as well as the psychological status improve
[6]. After the intervention, it seems to be difficult for many children to maintain the skills they have acquired and to continue with weight reduction or stabilization at home, especially if no follow-up therapy is provided
[6].

This raises the question which factors are crucial for the development of obesity, as well as which factors play significant roles in successful weight loss and weight loss maintenance in children and adolescents.

### Predictors of obesity, weight loss and weight loss maintenance

Different attempts have been made to identify potential predictors of weight loss and weight loss maintenance in the past
[7-10]. Besides epigenetic and genetic approaches, these strategies can be subdivided into four clusters of investigations depending on the main focus of the researchers and research groups. These clusters include 1) demographic, psychometric and sociometric data, 2) objective and subjective parameters of physical condition, 3) autonomic nervous system regulated functions and 4) objective and subjective parameters of eating behavior. In most cases, interest has been limited to variables within one cluster rather than across clusters.

In addition, clinical variables such as actual weight, diagnosis, comorbidities
[11], medication
[12], metabolic status (e.g. fasting glucose levels and glucose tolerance)
[13], and endocrine variables
[14,15] have frequently been used to try to predict success of dietary management, but yielding little predictive ability. Often, a number of predictors are associated with obesity. Most often these include psychological, but rarely physiological
[14], psycho-physiological
[16] or neurocognitive functions
[17]. Furthermore, few of these predictors have been studied for their predictive value of weight reduction and weight loss maintenance as part of inpatient or outpatient treatment.

#### Demographic, sociometric and psychometric predictors

It is known that in general the social environment of the child plays a crucial role in weight control
[18,19]. This applies to aspects such as ethnic origin
[20], income
[21], health of parents
[22] as well as their eating habits
[23]. The EvAKuJ study showed - in a sample of 1916 overweight and obese children and adolescents - that in inpatient treatments only the BMI at admission was predictive of the short and long-term treatment success, whereas gender, all collected psychosocial variables and the parental BMI played no significant role
[24].

#### Subjective and objective parameters for body condition

The total energy requirement of an organism is made up of the resting energy requirement, the activity dependent energy consumption, and food-induced thermogenesis
[25]. This balance is substantially altered in adult obesity
[26] and potentially in children as well
[27].

An increase in physical fitness has a positive effect on body composition and weight, which has also been shown for children during an inpatient treatment for weight loss
[28].

In childhood, sleep duration appears to have a significant impact on body composition. Gonnissen and colleagues (2013) showed an inverse correlation between changes in BMI and changes in sleep duration in puberty which resulted in neuroendocrine variations during adulthood. These variations were reflected in a positive energy balance with a coexistence of sleep disturbance
[29]. Furthermore, it could be shown that increased sleep duration and an increase in physical activity were associated with positive changes in sleep behavior in inpatients during weight reduction
[30].

It was recently shown in young people that parents, peers, media, and religious influences have an impact on the nature and extent of body satisfaction and influence the type and amount of consumed food and the frequency of physical activity
[31-33]. Disturbances of body image are frequent in eating disorders
[34] and also affect other parts of body awareness
[35]. Sarisoy and colleagues (2012) compared obese individuals to healthy controls and found negative correlations between self-esteem, body image, and harm avoidance scores, and a positive correlation between body image and self-directedness in the obese population
[36]. As yet, only few studies investigated the development of body image disturbances in children and report controversial results
[37].

Disordered interoception (perception of intrinsic bodily sensations, e.g. hunger and satiety) has been reported as a secondary marker of diseases such as cancer cachexia and depression in the elderly. An interoception test (Schandry
[38]) should allow investigating whether increased body weight and therapy changes are associated with bodily perception and whether these parameters influence the course of weight loss or regain.

#### Autonomic nervous system regulation

The autonomic nervous system (ANS) controls the maintenance of the balance of vital functions such as breathing, heart rate, and digestion and plays a crucial role in the regulation of acute and chronic stress responses
[39]. BMI has a direct influence on heart rate variability (HRV) at rest and during exercise
[40,41] and during fasting in healthy subjects
[42]. Patients with obesity often show a changed balance between the (decrease) activity of the parasympathetic and the (increased) sympathetic nervous system
[43] that normalizes after weight loss
[44]. Another potentially relevant measure of ANS activity is the electrogastrogram (EGG) recording gastric myoelectrical activity
[45,46] closely associated with cardiac HRV
[47].

Psychosocial stressors such as parental divorce
[48,49], poor mental health of parents
[50,51] or of children themselves
[52,53], are often associated with negative health outcomes
[54-56], but appear to act as moderators rather than mediators of weight-loss. To our knowledge, the ANS response to acute (experimental) stress
[57] has not been evaluated as a potential predictor of weight-loss and weight-loss maintenance in children and adolescents.

#### Subjective and objective measures of eating behavior

Smell and taste are often altered in patients with eating disorders and obesity, even in children
[58,59], but data are controversial. It is not clear whether children who participate in weight loss programs have pathological sensory thresholds and whether these changes are normalized after treatment.

In obese children, hyperactivity of the limbic and paralimbic brain areas was observed during presentation of food stimuli in the hungry state. These areas remain activated after a meal and after the presentation of food stimuli
[60]. It is not clear whether and how processing of food stimuli plays a role in weight loss treatment.

When subjects were asked to fill the same amount of water in a low, wide glass and in a tall, narrow one tend to fill more water in the low, wide glasses due to an optical illusion
[61,62]. This implies that the estimation of food portion sizes may be affected by their visual appearance
[61,62]. It is not known whether the number of correct/incorrect estimates of quantities of food and liquids is different in our study population and whether this has an impact on prediction of weight loss and weight maintenance.

An indirect measurement of eating behavior is the eating rate (run of a spoon or a fork to the mouth per time unit)
[63]. Moreover, an increased eating rate may be associated with excess weight
[64]. It was shown
[65] that the movement of eating is different to other accidental or deliberate motor activities of the dominant hand or arm. On this basis, a device was developed called "bite-counter"
[66] which can measure the eating rate. The bite-counter had not been evaluated in children and adolescents.

While the list of potential measurements within and across these clusters is virtually unlimited, their selection can be determined based on two criteria: a) feasibility in a pediatric inpatient setting at the beginning and the ending of a therapy within a limited time frame, and b) having been shown previously to bear relevance in (childhood and adolescent) obesity.

## Methods/Design

### Aims of the study

The aim of the study is to identify potential pre-treatment predictors of successful weight loss in obese children and adolescents during a standardized therapeutic treatment in an inpatient rehabilitation setting. In addition, repeated measures of the same variables at the end of treatment may demonstrate whether psychophysiological measures that respond to weight loss are associated with therapy success and whether they may serve to predict long-term weight-loss maintenance at follow-up. In addition, clinical parameters will be taken from the hospital charts and examined as potential predictor variables. We are aware that for some of the collected parameters the time span between measures may be too short. Therefore, follow-up studies are planned for evaluating the success of intervention.

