### Outcomes

#### Primary outcome

The primary outcome measure is the change of the body mass index standard deviation score (BMI-SDS)
[68]. SDS values indicate how many standard deviations an individual’s BMI lays above or below an age and gender matched median of BMI, a deviation of the value about two standard deviations above (+2) corresponds to the 97.7 percentile of the reference group
[69]. Reference data for German children are used
[67]. In order to calculate the BMI, the body weight and body height will be measured upon admission and upon discharge of their inpatient stay using calibrated instruments.

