### Statistics

We expect measures to be highly correlated within each cluster, and some variables within each cluster to be more sensitive or predictive to weight-loss during treatment than others. These key variables have been used as predictors for sample size calculation.

Cluster 1: Key variable: self-esteem scale according to Rosenberg

Cluster 2: Key variable: agility/motor activity (Dordel-Koch test)

Cluster 3: Key variable: ECG/IBI response to stress

Cluster 4: Key variable: caloric intake per time unit

To calculate optimal sample size, G*Power 3.1.7
[102] was used. To analyze the main research question (prediction of weight loss maintenance by key variables), sample size was derived for r^2^ deviation from zero (F distribution, Linear multiple regressions: Fixed model, R^2^ deviation from zero). Correlations of r = .3 (medium effect size
[103]) were assumed for predictor-outcome associations as well as the predictor‘s intercorrelation matrix, resulting in a squared multiple correlation of r^2^ = .189 and an f^2^ = .234. With a level of significance at alpha = .05 and a statistical power (1-beta) of .8, a sample size of 57 would be optimal to decide on the predictive quality of the model.

Statistical analysis will be conducted in two steps: variables within each cluster will be tested for their intercorrelation, their responsiveness to weight change, and for their ability to predict weight loss in a one-by-one fashion (step 1). In cases of high within-cluster intercorrelation (as predicted), a hierarchical model will be constructed with the most sensitive variable per cluster to be entered into a multivariate regression model (step 2).

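### For measures taken at discharge, the plan has no step that separates prediction of maintenance from a restatement of the weight already lost in the clinic

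*Protocol article*

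**What the plan says.** The Aims of the study section first looks for pre-treatment predictors of weight loss. It then turns to the measures repeated at the end of the stay and asks whether "psychophysiological measures that respond to weight loss are associated with therapy success and whether they may serve to predict long-term weight-loss maintenance at follow-up".

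The Statistics section opens its sizing with "To analyze the main research question (prediction of weight loss maintenance by key variables". It names one key variable per cluster: self-esteem, motor performance, the cardiac response to stress, and caloric intake rate. Correlations of .3 "were assumed for predictor-outcome associations as well as the predictor‘s intercorrelation matrix". The protocol reports the effect size that follows from this as "resulting in a squared multiple correlation of r^2^ = .189 and an f^2^ = .234". Its conclusion on the number of children is that, for "a level of significance at alpha = .05 and a statistical power (1-beta) of .8, a sample size of 57 would be optimal".

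The analysis has two steps. Step 1 looks at how the variables in each cluster correlate with one another and also examines "their responsiveness to weight change, and for their ability to predict weight loss in a one-by-one fashion (step 1"). Where the within-cluster correlation turns out to be high, step 2 applies, in which "a hierarchical model will be constructed with the most sensitive variable per cluster to be entered into a multivariate regression model (step 2").

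The values needed for an adjustment will exist. Under Primary outcome, "the body weight and body height will be measured upon admission and upon discharge of their inpatient stay using calibrated instruments".

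**The concern.** A discharge measure of interest because it responds to weight loss will be correlated with the loss. If the loss in the clinic is itself related to the result at follow-up, in either direction, the measure will be associated with that result through the loss alone. Step 1 adds to this because responsiveness to weight change is one of its screening criteria. Step 2 then names no weight term.

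The protocol's own Background makes the path plausible. It reports that the autonomic imbalance seen in obesity returns to normal once weight is lost, and an autonomic response is the Cluster 3 key variable. It also cites an inpatient study in which admission BMI alone predicted short- and long-term success.

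What is at stake is the use proposed in the Discussion, namely screening instruments for tailoring therapy. A test that repeats what the discharge weight already shows has little value for that, and the described analysis would not reveal it.

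**Working it through.** **1. The plan's own figure.** With k predictors, each correlated r with the outcome and ρ with each other, R² = k·r² / (1 + (k − 1)·ρ).
- For k = 4 and r = ρ = .3: R² = .36 / 1.9 = .1895, and f² = .1895 / .8105 = .234. Both match the protocol.
- Non-central F with 4 and 52 degrees of freedom and noncentrality .234 × 57 = 13.3 gives power .809. The stated 57 is reproduced.
- For k = 3, R² = .27 / 1.6 = .169. For k = 5, R² = .45 / 2.2 = .205. Of these, only four predictors give .189, and the four named key variables fill those places. None is BMI-SDS or its change.

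**2. A measure that only mirrors the loss.** Let M be the discharge measure, L the in-stay loss and Y the follow-up result. Write a for the correlation of M with L and b for that of L with Y, with no direct path from M to Y. Then the correlation of M with Y is a × b. The protocol gives neither a nor b, so the values are assumed. Rates come from simulation: 20,000 runs per row, N = 57, two-sided .05.

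| a | b | a × b | M significant, L not in model | M significant, L in model |
|---|---|---|---|---|
| .3 | .3 | .09 | 10% | 5% |
| .5 | .3 | .15 | 20% | 5% |
| .5 | .5 | .25 | 47% | 5% |
| .7 | .7 | .49 | 98% | 5% |

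The overall F test of four such measures behaves alike. Without L it rejects in 11% of runs at a = b = .3 and 99.5% at a = b = .7. With L in the model it rejects in about 5%.

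**3. What adjustment does to power.** Add L as one covariate, correlated .3 with each of four measures and ρ with the outcome. Keep all other correlations at .3. After removing L:
- covariance of each measure with the outcome: c = .3 − .3ρ
- variance of each measure: 1 − .09 = .91
- covariance between two measures: .3 − .09 = .21
- R² added by the four: 4c² / (.91 + 3 × .21) = 4c² / 1.54
- partial f²: added R² / (1 − ρ² − added R²)

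At ρ = .3: c = .21, added R² = .1145, f² = .1145 / .7955 = .144. Power is 57% at N = 57 and 60% at the planned 60 children. N = 88 is needed for 80%.

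At ρ = .5: c = .15, added R² = .0584, f² = .0584 / .6916 = .0845. Power is 35% at N = 57.

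**The case against.** **This is a condensed article.** It does not exclude weight terms. Cluster 2 includes anthropometry and a scale weight, the same sessions are repeated before discharge, and chart parameters are to be examined as potential predictors. The article also does not say whether step 2 uses admission values, discharge values or changes. A reader might infer that weight is barred from the model; the text does not support that. What stands is narrower: nothing makes a weight term part of the maintenance model, and the selection rule and sizing that are stated point to four other variables.

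**The aim is prediction, not mechanism.** A measure that mirrors the loss does predict maintenance, with a true correlation of a × b. A reader might call the 10% to 47% false-positive rates. They are not type I errors for the aim as worded. They are the rates at which a measure with no contribution beyond the loss would be reported as a predictor.

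**Adjustment can do harm.** For an admission measure, the in-stay loss comes later and may lie on the path to maintenance. Adjusting for it would remove the part of the effect that acts through initial loss. This objection stands in full and limits the fix to discharge values and changes.

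**Adjustment might be expected to gain power.** If the weight covariate were unrelated to the measures, power would rise from 80.9% to 85.7% (covariate-outcome correlation .3) or 93.7% (.5). The concern presupposes that the measures do track the loss. Under that premise power falls, as step 3 of the working shows.

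**Conclusion.** The point holds in limited form. Followed as described, the plan cannot show whether a discharge measure tells more about later maintenance than the weight already lost. That a mirror measure will be declared a predictor would be too strong a reading; it can be. At N = 57 the chance is about 10% with both correlations at .3, 20% with .5 and .3, and 47% with both at .5, against 5% with the in-stay loss in the model. These figures rest on assumed correlations, on a measure with no direct path to the outcome, and on follow-up data from all 57 children. The admission predictors of the first aim are not affected.

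**What to change.** Limit the change to analyses in which values or changes measured at discharge predict maintenance:

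- Report the unadjusted association, as now.
- Beside it, fit a model with discharge BMI-SDS and the admission-to-discharge BMI-SDS change as a fixed first block, and report the R² the measure adds.
- Claim prediction beyond the weight already lost only on that increment.
- State for each maintenance model whether admission values, discharge values or changes are used, and do not force the in-stay change into the analysis of admission predictors.

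No new data are needed. The cost is two degrees of freedom and lower power. The 57% applies to the four-variable block with one weight covariate and all correlations .3; the proposed first block has two. The plan should say that the stated 80% does not apply to the increment test. It should then either recheck the sample size for that test or label it exploratory and report it with confidence intervals.

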### Study population

#### Patients and the inpatient setting

The obesity therapy concept at the Children Rehabilitation Hospital for Respiratory Diseases, Allergies and Psychosomatics, Wangen i.A., Germany is aimed at recovery from comorbid diseases associated with obesity, rediscovering joy of life, developing a forward-looking perspective, independent living, and growing up unencumbered. The children and young people are treated in accordance with the latest developments in medicine, especially pediatrics and in close cooperation with regional educational institutions such as the obesity academy (Adipositas-Akademie Baden-Württemberg e.V.), an atopic dermatitis academy (Neurodermitisakademie München/Wangen/Gaißach) and an asthma academy (Asthmaakademie Baden-Württemberg e.V.). Infants, children and adolescents are housed and cared for in small therapeutic groups with peers of the same age and in residential units situated on a park-like hospital ground. The clinic has its own kindergarten and a school with regular classes for all types of curricula.

Pediatricians, allergists, psychologists, social workers and nursing staff, teachers, trainers, dietetic professionals, occupational and speech therapists and staff for physical therapy work together as one team. The special obesity training is an integral part of therapy. The individual modules of the training are rooted in the concept of the clinic, including exercise and sports, change to a healthy diet, and weight-loss.

The nutrition concept is based on a balanced diet or “optimized mixed diet”. In nutrition training, patients meet weekly in small groups of 6–8 age-matched participants. In a training kitchen, all children and adolescents learn how to prepare food and cook with the aim of proper food handling and preparation when they return home. Additionally, they complete "shopping training" in a supermarket.

The hospital treats approximately 200 obese children and adolescents per year. The average duration of stay is 42 days.

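### Children are housed and trained in small same-age groups, but the regression and N = 57 assume independent children; the likely effect is small and a group term would deal with it.

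*Protocol article*

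**What the plan says.** The protocol article, under Patients and the inpatient setting, describes care and training in groups: "Infants, children and adolescents are housed and cared for in small therapeutic groups with peers of the same age". For one module it gives a size: "In nutrition training, patients meet weekly in small groups of 6–8 age-matched participants". These groups contain all patients, not only study children. The same section gives a throughput of about 200 obese patients a year, and the Abstract plans to recruit 60 over one year.

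The Statistics section names four key variables, one per cluster of measurements, and says "These key variables have been used as predictors for sample size calculation". The model is "Linear multiple regressions: Fixed model, R^2^ deviation from zero". The inputs are "Correlations of r = .3 (medium effect size") for predictor with outcome and between predictors, "resulting in a squared multiple correlation of r^2^ = .189 and an f^2^ = .234". The result is "With a level of significance at alpha = .05 and a statistical power (1-beta) of .8, a sample size of 57 would be optimal".

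Within-group correlation is not mentioned. In that section, cluster means a set of measurements and not a group of children. The hierarchical model of step 2 concerns which variable per set enters the regression; nothing there describes a group-level term.

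**The concern.** The setting and the calculation do not match. Members of a residential or training group share a period of their stay and group sessions, so their weight change may be correlated. The primary outcome, change in BMI-SDS from admission to discharge, accrues during this group-delivered stay.

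The groups are also formed by age, across an eligible range of 9 to 17 years. A predictor that varies with age will therefore be more alike within groups than between them. Motor performance is a likely example, and caloric intake per time unit may be another.

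When both sides of a regression are correlated within groups, ordinary standard errors are too small. A group effect on weight loss can then look like a child-level predictor, and finding child-level predictors is the aim of the study. The same mechanism acts on the one-by-one tests of step 1 and on the regression of step 2.

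**Working it through.** **1. The plan's own figure.** With four predictors and all correlations .3:
- R² = 4 × .3² / (1 + 3 × .3) = .36 / 1.9 = .189
- f² = .189 / (1 − .189) = .234 (unrounded .2338)
- The noncentral F with 4 and N − 5 degrees of freedom and λ = f² × N gives power .809 at N = 57 and .833 at N = 60.

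N = 57 is the smallest N reaching .8 with unrounded f², so the stated figure reproduces.

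**2. Study children per group.** The study enrols 60 / 200 = 30% of patients. A group of 6 to 8 then holds .30 × 6 = 1.8 to .30 × 8 = 2.4 study children on average. A year gives about 200 / 7 ≈ 29 groups of seven. How study children are actually spread over groups is not stated.

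**3. Approximate effect on one slope.** With m study children per group, the variance of an ordinary slope estimate is multiplied by about 1 + (m − 1) × ICC(predictor) × ICC(outcome). At the upper assumed ICCs, .3 and .2:
- m = 2: 1 + 1 × .06 = 1.06. A nominal 5% two-sided test then uses 1.96 / √1.06 = 1.90, a true level of about 5.7%.
- m = 7: 1 + 6 × .06 = 1.36. The cut-off becomes 1.96 / √1.36 = 1.68, a true level of about 9.3%.

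If either ICC is zero, the factor is 1.

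**4. Simulation of the planned four-predictor F test.** N = 57, shared group effects in all four predictors and in the residual, 40,000 runs per setting. The ICCs are assumptions. True alpha at nominal .05:

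| ICC outcome / predictors | 2 per group | 57 scattered at random over 29 groups | 7 per group |
|---|---|---|---|
| 0 / 0 | .048 | .049 | .051 |
| .2 / 0 | .051 | .050 | .050 |
| .05 / .1 | .053 | .051 | .055 |
| .1 / .1 | .051 | .051 | .060 |
| .1 / .3 | .055 | .061 | .079 |
| .2 / .2 | .057 | .061 | .093 |
| .2 / .3 | .062 | .071 | .118 |

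The Monte Carlo standard error is about .001.

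**5. Power.** In the same settings the ordinary test's rejection rate under the planned alternative is .78 to .79 at N = 57, with or without clustering, and .80 to .82 at N = 60. It lies below .809 because the simulation draws predictors at random and does not hold them fixed; clustering is not the cause.

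Part of that rejection rate is bought with an alpha above .05. With the critical value reset so that true alpha is .05 (20,000 runs per setting), power goes from .784 without clustering to .759 at two per group with outcome ICC .2 and predictor ICC .3. Over the settings with about two per group, the lowest value is about .74.

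**The case against.** A reader might infer that the stated alpha of .05 and power of .8 simply do not hold, or that N needs the usual design effect. For seven per group and an ICC of .05 that would be 1 + 6 × .05 = 1.3, and 57 × 1.3 = 74.1, so 75 children. The documents support neither reading. That design effect applies to exposures that are constant within a group, whereas the key predictors are measured on each child and vary within groups. Alpha moves only if outcome and predictors both have a sizeable ICC, and the document gives neither.

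Other points reduce the likely size:
- BMI-SDS is already standardised for age and sex, which limits an age-driven correlation in the outcome. It does not remove a group effect on change.
- Baseline measures are taken in the first week, before much shared treatment.
- The Statistics section names weight loss maintenance as the question for N. That is assessed after discharge, when group effects may be weaker.
- Not all four predictors need cluster. With a predictor ICC of .5 on one predictor only and an outcome ICC of .1 to .2, alpha is 5.5% to 5.6% at two per group and 6.5% to 8.3% at seven.
- The group size of 6 to 8 is given for one weekly module, and fixed membership is not stated.

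These points stand and keep the matter minor. A condensed article may also leave the handling of groups to a fuller document that is not shown, so the absence of a group term is not in itself an error. What remains is that the stated calculation assumes independence in a setting described as grouped. The size of the residential units is not given, and enrolment depends on available time slots, so groups with more than two study children cannot be excluded.

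**Conclusion.** The concern holds as a minor point. N = 57 is computed correctly, but it rests on independence that the described setting does not assure.

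Under assumed ICCs of .1 to .3 for the predictors and .05 to .2 for the outcome, true alpha is about 5% to 7% with about two study children per group, the number that the article's own figures imply. It is roughly 6% to 12% only if whole groups of seven enrol. The ordinary test's rejection rate does not fall. Power at a true 5% alpha ranges from practically unchanged down to about .74 with two per group, against about .78 without clustering. No increase in sample size follows from this.

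**What to change.** Record each child's therapy group and residential unit at admission, together with any later change. Add a random intercept for group to the step 1 and step 2 regressions, or report that model as a sensitivity analysis beside the ordinary one. State in the Statistics section that the alpha of .05 and power of .8 at N = 57 assume no within-group correlation.

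In a check of 1,500 runs per setting, with predictor ICC .5, outcome ICC .1 to .2 and two to seven study children per group, a random-intercept model held the error rate at 4.3% to 7.1%. Ordinary regression in the same settings gave 5.6% to 16.8%. The gain is small at two per group and larger if groups turn out fuller.

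The cost is one extra variable, a sentence or two of text and slightly less favourable p-values. No additional patients or procedures are needed. If the identifier is not recorded during the study, the check will be hard to make later.
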